**Fig. 2 Fig2:**
[figure not shown]
Enrollment, intervention, and assessment in the ELEMENT trial

The investigator’s research personnel are responsible for entering all criteria on randomize.net which will then generate the randomization sequence. The research personnel involved in the statistical analysis and patients, but not the endoscopists, are blinded to treatment allocation. To ensure the quality of the trial, unblinding will occur only in exceptional circumstances when knowledge of the treatment allocation is essential for the optimal management of the patient.

### Treatment protocol

Treatment allocation is to EUS-CDS with LAMS vs. insertion of a traditional transpapillary metal stent at ERCP. All procedures are performed by experienced endoscopists with or without trainee involvement. Following informed consent, procedures are either performed under conscious sedation or general anesthesia, as per existing institutional procedural protocols.

#### EUS-BD

A curvilinear endoscope is inserted orally and advanced to the duodenal bulb. Biliary accessibility is then confirmed via EUS from the duodenal bulb and with Doppler to rule out any intervening vessels. In order to maintain stability in the duodenal bulb, the long endoscope position is used when possible. A LAMS (Axios™, Boston Scientific, Marlborough, MA, USA) is then inserted with cautery assistance without tract dilation and deployed under EUS guidance from the duodenal bulb. The choice of stent size is at the discretion of the endoscopist (8 × 8 mm or 6 × 8 mm).

#### ERCP

A duodenoscope is advanced orally to the papilla. The bile duct is then cannulated with a sphincterotome using the guidewire-assisted technique. A cholangiogram is then performed followed by insertion of a self-expanding metal biliary stent. The performance of a biliary sphincterotomy prior to stent insertion and the choice of stent size (10 × 40 mm, 10 × 60 mm, 10 × 80 mm) and stent type (partially covered, fully covered, or uncovered) are recorded and left to the discretion of the endoscopist.

The assigned procedure (EUS-BD or ERCP) will be aborted in case of technical failure including inability to reach the papilla or cannulation failure in case of ERCP and inability to obtain a safe window for LAMS insertion in EUS-BD. A medical effectiveness approach is adopted, allowing additional procedures deemed indicated by the treating team (ERCP, EUS-BD, percutaneous drainage, and/or surgery) following the initial procedure in both groups, which will be recorded.

### Endpoints

The primary endpoint is the rate of stent dysfunction (including both migration and occlusion) needing endoscopic or radiological re-intervention (Table 2). Patients who reach the primary endpoint are considered to have completed the study once hospitalization time for stent dysfunction and delays in chemotherapy treatment have been captured. Patients who do not reach the primary outcome are followed until surgery, death, or up to 1-year post stent insertion.

**Table 2 Tab2:** Criteria for primary endpoint of stent dysfunction

Meeting one or more of the following criteria:	
□ Suspected cholangitis [13]	
□ Definite cholangitis [13]	
□ 50% increase in bilirubin from the lowest level post index procedure	
□ 20% increase in bilirubin from the lowest level post index procedure AND evidence of obstruction on imaging (US/CT/MRI)	
AND:	
□ Endoscopic or radiological re-intervention confirming stent blockage or migration needing stent cleaning, stent change, and/or additional stent insertion

**Table 3 Tab3:** Secondary endpoints

1. Technical success defined as successful insertion of a transpapillary stent or choledochoduodenostomy stent at the initial procedure at time of randomization [6–8]	
2. Clinical success defined as 50% decrease in bilirubin < 2 weeks post-stent insertion or less than 25% of pre-procedure bilirubin level within 4 weeks post stent insertion [6]	
3. Stent patency defined as mean time to stent obstruction or migration (patient will be censored at last-follow-up or death)	
4. Proportion of patients with interruptions in chemotherapy treatment due to recurrent stent dysfunction	
5. Early adverse events (within 14 days of index procedure) as defined per the ASGE lexicon for endoscopic adverse events [18], including post-procedural pancreatitis, bleeding, intestinal perforation, and cholangitis	
6. Delayed adverse events (greater than 14 days of index procedure until last follow-up or death)	
7. Cost-effectiveness analysis	
Additional outcomes	
1. Median number of days in delayed chemotherapy treatment if interrupted	
2. Procedure time defined as from insertion of the endoscope to endoscope withdrawal1	
3. Fluoroscopy time	
4. Rate of hospitalization and length of stay	
5. Mortality	

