### Data collection

Collected data include primary, secondary (Table 3), and additional endpoints listed above, demographics, ASA score, Karnofsky index, type of sedation used, laboratory investigation including complete blood count, coagulation profile, liver enzymes, tumor staging based on the TNM classification for pancreatic cancer, quality of life data using the EQ-5D, peri-endoscopic data such as use of rectal indomethacin, antibiotics, and technical details including type of endoscope, EUS and ERCP accessories including stent type and size, sphincterotomy or tract dilation performed prior to stent insertion. Data are collected at the index procedure, and also at days 7, 30, 90, 180, 270, and 1 year post-randomization.

All data will be collected by research personnel who have been previously trained to use both the randomization website (randomize.net) and the data capturing software (redCAP). These research personnel are also GCP (Good Clinical Practices) and SOP (Standard Operating Procedures) certified. All data collected will be de-identified, meaning that information such as name, date of birth, hospital identifier, and Medicare number will not be stored in the main database. Each participant will be referred to by their study number. There will be a separate file stored in a password protected and encrypted computer with the decoder of identifiables in case these patients need to be contacted. All data will be stored for 7 years after publication or as requested in Standard Operating Procedure (SOP) from individual sites. Only data relevant to the study as outlined in this protocol will be collected by the research team. All information collected during the research project will remain confidential.

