### Follow-up

All patients are followed until either the primary outcome, surgery, death, or a total of 1-year post stent insertion have been reached, whichever comes first. A medical effectiveness approach is adopted, allowing additional therapeutic approaches deemed indicated by the treating team following the initial procedure in both groups, and are recorded.

Follow-up will be conducted over the phone and at subsequent office visits. If the patient is unable to be reached, a letter will be sent to their residence requesting a call back to the research assistant. A chart review can be performed in the event a patient is not able to be reached within a 2-week window of the follow-up date. If follow-up information is unable to be obtained, the patient will be considered a loss to follow-up and their data will documented accordingly. Any patient who deviates from the protocol or withdraws their consent from the ELEMENT trial at any point will be considered a protocol deviation and will be withdrawn from the data monitoring.

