##### Primary endpoint

Rate of re-intervention: Based on RCT data and retrospective series using LAMS [6–8, 10–12], we estimate a re-intervention rate of 30% vs. 10% for the ERCP and EUS-BD groups, respectively up to a 1-year follow-up period. To achieve a statistical power of 80% with a two-sided type I error of 5%, a total of 124 patients (62 in each arm) is required. Taking into account a 5% dropout rate, a final sample of 130 patients (65 patients in each arm) is needed.

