### Analyses

An intention-to-treat analysis along with a secondary per-protocol analysis will be carried out. Descriptive statistics will assess the adequacy of patient characteristics and balancing of the randomization process. Inferential analysis will employ Student’s *t* test and Chi-square testing. Survival analysis using the Kaplan–Meier method will be used to assess stent patency time. A step-wise multivariate regression analysis will be undertaken to identify independent predictors of stent dysfunction and adverse events using a log-rank test. A *p* value of 0.05 or less will be considered statistically significant. All analyses will be performed using SAS version 9.4. No interim analysis is planned given the short accrual time, relative small sample size, and short follow-up period.

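### Stent patency is fixed as a mean time with no restriction point, so at the planned event rates the figure will depend on an unstated cut-off; one minus Kaplan–Meier should not be read as the proportion with dysfunction

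*Protocol article*

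**What the plan says.** Table 3 of the protocol article (Endpoints) fixes both the summary measure and the censoring rule for secondary endpoint 3: "Stent patency defined as mean time to stent obstruction or migration (patient will be censored at last-follow-up or death". The Analyses section names the estimator: "Survival analysis using the Kaplan–Meier method will be used to assess stent patency time". No restriction time, quantile or competing-risk method is given.

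The Follow-up section says "All patients are followed until either the primary outcome, surgery, death, or a total of 1-year post stent insertion have been reached, whichever comes first". Surgery is not named in the Table 3 censoring rule, but because it ends follow-up, a patient who has surgery is censored there as well.

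The only event rates given are those behind the sample size: "we estimate a re-intervention rate of 30% vs. 10% for the ERCP and EUS-BD groups, respectively up to a 1-year follow-up period".

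**The concern.** The mean of a survival distribution is the area under its whole curve. When follow-up stops at 1 year and most patients have had no event, the curve stops well above zero and the rest of the area is unknown. Software still prints a number, but only after cutting the curve somewhere. If the cut differs between arms, the arm with fewer events tends to be cut earlier and loses area because it did better.

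There is also a question of reading. Death and surgery end the chance of observing dysfunction. With both censored, one minus Kaplan–Meier does not estimate the share of patients who experience dysfunction. A reader who sets that curve beside the primary endpoint proportions would see larger figures and a larger gap between arms.

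At stake is the interpretation of a secondary outcome that the abstract and the Discussion both list (time to stent dysfunction).

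**Working it through.** **Inputs.** From the protocol article: 30% v 10% to 1 year, 65 patients per arm, follow-up of at most 1 year. Assumed: constant hazards, and a 1-year death or surgery rate *q*, which the documents do not give and which is therefore varied.

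1. **The plan's own figure.** Two proportions, two-sided 5%, 80% power, no continuity correction: n = [1.96·√(2·0.2·0.8) + 0.8416·√(0.3·0.7 + 0.1·0.9)]² / 0.2² = (1.109 + 0.461)² / 0.04 = 61.6, so 62 per arm. This reproduces the stated 124, so the rates can be taken at face value.

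2. **Share without the event.** 65 × 0.30 + 65 × 0.10 = 19.5 + 6.5 = 26 events in 130 patients. So 104/130 = 80% have no event (70% ERCP, 90% EUS-BD).

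3. **The unrestricted mean.** With no deaths or surgery the curves stand near 0.70 and 0.90 at 12 months, and not even the median is reached. Extrapolating with λ = −ln(0.70) = 0.357 and λ = −ln(0.90) = 0.105 per year gives means of 12/λ, about 34 and 114 months. Nearly all of that lies beyond the 12 months observed.

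4. **Mean to a common 365 days, no deaths or surgery.** 365·(1 − e^−λ)/λ = 365 × 0.30/0.357 = 307 days (ERCP) and 365 × 0.10/0.1054 = 346 days (EUS-BD), a difference of 39 days.

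5. **Mean cut at each arm's own last event.** With *k* events spread roughly evenly over the year, the last falls on average near 365·k/(k+1): 365 × 19.5/20.5 = 347 days (ERCP) but 365 × 6.5/7.5 = 316 days (EUS-BD). The better arm loses about a month. Simulation (4,000 trials, 65 per arm):

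| Assumed death or surgery by 1 year | Cut at own last event, EUS-BD v ERCP (days) | Wrong direction | Common 365 days, EUS-BD v ERCP (days) | Wrong direction |
|---|---|---|---|---|
| None | 295 v 291 | about 37–38% | 346 v 307 | under 0.5% |
| 50% | about 275 v 265 | about 37% | 339 v 285 | under 0.5% |

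Repeat runs at 50% gave 273 to 276 days for EUS-BD. The 365-day figures censor death and surgery.

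6. **One minus Kaplan–Meier against the actual proportion.** Let μ = −ln(1 − q). Solve λ/(λ+μ)·(1 − e^−(λ+μ)) = p for p = 0.30 and p = 0.10, so that the actual 1-year proportion stays at the planned value. Then one minus Kaplan–Meier is 1 − e^−λ. For q = 0.50, μ = 0.693 and λ = 0.517 (ERCP) and 0.148 (EUS-BD).

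| Assumed q | ERCP (actual 30%) | EUS-BD (actual 10%) |
|---|---|---|
| 0 | 30% | 10% |
| 30% | 35% | 12% |
| 50% | 40% | 14% |
| 70% | 48% | 17% |

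**The case against.** The strongest reply is that follow-up is capped at 1 year in both arms, which offers a natural common horizon. A mean taken to that horizon is estimable and behaves well, and a truncation time is often left to an analysis plan, which is not shown here. This stands in part. Only the unrestricted mean fails, and cutting at each arm's last event is a convention the protocol does not adopt. A reader might infer that the patency comparison will vanish or reverse; the documents do not support that, since the reversal rate holds only under that convention, and even then the average direction is right. What does not stand is that this is merely absent detail: Table 3 itself chooses an unqualified mean.

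The second reply is that censoring at death is a legitimate view of device patency. This stands. A log-rank or cause-specific comparison with death censored is valid as such. A reader might infer that Kaplan–Meier will overstate dysfunction, but the protocol nowhere says that one minus Kaplan–Meier will be reported as the share needing re-intervention. That share is the primary endpoint. The two quantities differ by construction, so the excess is an error only if one is read as the other.

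A reader might also see a conflict in the time origin, because follow-up ends 1 year after stent insertion while data are collected "also at days 7, 30, 90, 180, 270, and 1 year post-randomization". Table 3 states no origin for patency, and dysfunction is confirmed by a re-intervention that has its own date. No effect is shown, so nothing is claimed on this.

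**Conclusion.** The point holds in limited form. The mean as worded is not estimable at the protocol's own planned rates; this needs no assumption about mortality. The consequence depends on the cut-off: with each arm cut at its own last event, a threefold difference in dysfunction appears as about 4 to 10 days and is reversed in roughly 37% of trials. With a common 365 days it appears as 39 days (no deaths or surgery) to 54 days (50% assumed) and is reversed in under 0.5%. These sizes rest on constant hazards and the planned rates.

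For the Kaplan–Meier reading, the direction is certain wherever death or surgery precedes dysfunction. The size is not, because the documents give neither a mortality nor a resection rate; 35% v 12% to 48% v 17% is an assumed range. The 80% without the event is a planning expectation, and obstruction or migration may be slightly wider than dysfunction needing re-intervention.

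This is a secondary endpoint. The plan should be corrected, but neither the primary test nor the sample size rests on it.

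**What to change.** In Table 3, replace the mean time with the restricted mean time to stent dysfunction up to a common 365 days in both arms, and report the difference with its 95% confidence interval. State explicitly that death and surgery are censored, so that the result is understood as a cause-specific patency measure and not as time gained in the presence of death.

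In Analyses, add the cumulative incidence of dysfunction at 365 days with death and surgery as competing events (Aalen–Johansen estimate, Gray's test), and name it as the absolute-risk estimate that supports the primary endpoint. A log-rank or cause-specific comparison may stay beside it.

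The cost is a change of wording and slightly more analysis work. No new data are needed, since dysfunction, surgery and death already end follow-up.

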### Data collection

Collected data include primary, secondary (Table 3), and additional endpoints listed above, demographics, ASA score, Karnofsky index, type of sedation used, laboratory investigation including complete blood count, coagulation profile, liver enzymes, tumor staging based on the TNM classification for pancreatic cancer, quality of life data using the EQ-5D, peri-endoscopic data such as use of rectal indomethacin, antibiotics, and technical details including type of endoscope, EUS and ERCP accessories including stent type and size, sphincterotomy or tract dilation performed prior to stent insertion. Data are collected at the index procedure, and also at days 7, 30, 90, 180, 270, and 1 year post-randomization.

All data will be collected by research personnel who have been previously trained to use both the randomization website (randomize.net) and the data capturing software (redCAP). These research personnel are also GCP (Good Clinical Practices) and SOP (Standard Operating Procedures) certified. All data collected will be de-identified, meaning that information such as name, date of birth, hospital identifier, and Medicare number will not be stored in the main database. Each participant will be referred to by their study number. There will be a separate file stored in a password protected and encrypted computer with the decoder of identifiables in case these patients need to be contacted. All data will be stored for 7 years after publication or as requested in Standard Operating Procedure (SOP) from individual sites. Only data relevant to the study as outlined in this protocol will be collected by the research team. All information collected during the research project will remain confidential.

### Follow-up

All patients are followed until either the primary outcome, surgery, death, or a total of 1-year post stent insertion have been reached, whichever comes first. A medical effectiveness approach is adopted, allowing additional therapeutic approaches deemed indicated by the treating team following the initial procedure in both groups, and are recorded.

Follow-up will be conducted over the phone and at subsequent office visits. If the patient is unable to be reached, a letter will be sent to their residence requesting a call back to the research assistant. A chart review can be performed in the event a patient is not able to be reached within a 2-week window of the follow-up date. If follow-up information is unable to be obtained, the patient will be considered a loss to follow-up and their data will documented accordingly. Any patient who deviates from the protocol or withdraws their consent from the ELEMENT trial at any point will be considered a protocol deviation and will be withdrawn from the data monitoring.

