## Methods

### Design and objectives

The Eus-guided biliary drainage with LumEn apposing Metal stENT vs. ercp (ELEMENT) trial is a multicenter prospective randomized controlled trial, across nine sites in Canada, comparing EUS-CDS with a biliary LAMS vs. ERCP in the initial endoscopic management of malignant distal biliary obstruction (Fig. 1). We hypothesize that EUS-CDS using LAMS is associated with fewer episodes of stent dysfunction and need for re-intervention when compared to standard ERCP while being comparable in safety and technical success in patients with malignant distal biliary obstruction (Additional file 1). At the time of writing this manuscript, this trial has been approved by the IRB of the coordinating center and two additional participating sites. All other sites have submitted their IRB application and will only start patient recruitment once approved.

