#### Cost-effectiveness analysis

A decision tree will be created for the two possible biliary drainage approaches over a 6-month time horizon. Probability assumptions will be extracted from the RCT and the unit of effectiveness will be cost per QALY. Costs will be determined from chart data abstraction of patients in each group to determine resource consumption. The regie de l’assurance maladie du Quebec (RAMQ) and institutional database relating to professional fees, hospitalization (where appropriate), and equipment accounting for direct costs will be utilized. Third-party costs related to the procedure and downstream management costs will be determined based on the RCT resource utilization data. Deterministic and probabilistic sensitivity analyses will be undertaken to assess the robustness of the findings.

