## Discussion

The ELEMENT trial is a multi-center randomized trial designed to address the question of whether EUS-BD with LAMS is associated with fewer episodes of stent dysfunction and need for re-intervention compared to standard ERCP in the management of malignant distal biliary obstruction. This clinical trial will also compare the technical and clinical success, adverse events, time to stent dysfunction, and oncological outcomes such as interruptions in chemotherapy, rate of surgical attempt, and survival.

We recently completed a meta-analysis of randomized controlled trials (RCT) comparing EUS-BD vs. ERCP or EUS-BD vs. radiological percutaneous biliary tube drain insertion (PTBD) [14]. Overall, we identified three trials comparing EUS-BD to ERCP [6–8]. Technical and clinical success was similar between modalities; however, rates of re-intervention favored EUS-BD over ERCP (RR 0.40; 95% CI 0.29–094) and PTBD (RR 0.49; 95% CI, 0.28–0.88). In addition, EUS-BD was comparable in terms of safety to ERCP while demonstrating lower rates of adverse events when compared to PTBD (RR 0.59; 95% CI, 0.39–0.87). Although results from this meta-analysis are promising, the studies were single-centered and small, using mostly non-EUS dedicated devices.

The potential for less stent dysfunction requiring reintervention with EUS-BD over ERCP, if shown in our proposed trial, would be of great clinical significance not only because of the diminished morbidity in this often-frail patient population, but also because of the potential impact on oncological outcomes. For patients with metastatic pancreatic cancer with a good performance status, there is a clear survival benefit attributable to FOLFIRINOX therapy [15], which would be necessarily delayed if reinterventions are needed. Furthermore, there has been a push to give neoadjuvant chemotherapy [16, 17] even in resectable disease, meaning that the insertion of a reliable biliary stent that remains patent for longer is likely to become a cornerstone for optimizing oncological outcomes. From a practical efficiency (and perhaps cost-effectiveness) perspective, EUS also has the unique ability to achieve decompression and acquire precise tissue diagnosis at the same clinical setting.

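### Scheduled follow-up stops at the first stent dysfunction, so mortality, late adverse events, resection, EQ-5D and resource use are cut short about three times as often in the ERCP arm

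*Protocol article*

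**What the plan says.** Two sections of the protocol article set the stop rule, and they agree.

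- Follow-up: "All patients are followed until either the primary outcome, surgery, death, or a total of 1-year post stent insertion". The earliest of these ends observation.
- Endpoints: anyone with the primary endpoint is "considered to have completed the study once hospitalization time for stent dysfunction and delays in chemotherapy treatment have been captured". For the others, "Patients who do not reach the primary outcome are followed until surgery, death, or up to 1-year post stent insertion".

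Several planned comparisons need observation beyond that point.

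- Table 3 lists "Delayed adverse events (greater than 14 days of index procedure until last follow-up or death", and, as additional outcomes, hospitalization and mortality.
- The Abstract names the rate of surgical resection as a secondary outcome. The Discussion promises a comparison of "interruptions in chemotherapy, rate of surgical attempt, and survival".
- The Cost-effectiveness analysis section plans cost per QALY, with downstream costs taken from resource use in the trial. EQ-5D is listed under Data collection.

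The Primary endpoint part of the sample size calculation assumes re-intervention in 30% (ERCP) and 10% (EUS-BD) over up to 1 year. The Analyses section names the t test and chi-square test for inference, and Kaplan–Meier for stent patency only.

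**The concern.** The event that ends follow-up is the event the treatment is expected to prevent. The arm with more dysfunction is therefore observed for less time, and the imbalance grows the better the trial's hypothesis holds. The window for delayed adverse events is itself defined by last follow-up, so its length depends on the arm.

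The comparisons at stake are safety, survival, resection and cost per QALY. The Design and objectives section expects EUS to be comparable in safety, so a distortion in recorded deaths and late adverse events bears on a stated aim. An analysis plan cannot recover data that were never collected.

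**Working it through.** **The plan's own figure.** With 30% v 10%, two-sided 5% and 80% power, the mean proportion is 0.20 and the pooled-variance formula gives

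n = [1.96 × √(2 × 0.20 × 0.80) + 0.8416 × √(0.30 × 0.70 + 0.10 × 0.90)]² / 0.20² = (1.109 + 0.461)² / 0.04 ≈ 61.6, so 62 per arm.

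This reproduces the stated 62. The stated 65 per arm after 5% dropout is used below.

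**Patients cut short by dysfunction.** ERCP: 65 × 0.30 = 19.5. EUS: 65 × 0.10 = 6.5. The ratio is 3:1 and the total about 26.

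**Effect on recorded deaths.** The protocol gives no survival figure, so true 1-year mortality D is assumed equal in both arms and varied over 30%, 50% and 70%. Hazards are assumed constant, and death independent of dysfunction. Surgery exits are left out because no surgery rate is given.

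- Death hazard: m = −ln(1 − D).
- Dysfunction hazard l: solve l/(l + m) × [1 − exp(−(l + m))] = 0.30 (ERCP) or 0.10 (EUS).
- Observed years per patient: [1 − exp(−(l + m))]/(l + m).
- Recorded deaths: m × observed years.

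Example for D = 50%, m = 0.693:

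- ERCP: l = 0.517, observed 0.580 years (212 days), recorded deaths 0.693 × 0.580 = 40.2%.
- EUS: l = 0.148, observed 0.676 years (247 days), recorded deaths 0.693 × 0.676 = 46.9%.
- Without the dysfunction stop: 0.721 years (263 days) in both arms.

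| True mortality, both arms | l, ERCP / EUS | Recorded deaths, ERCP v EUS | Of 65 | Alive follow-up lost, ERCP v EUS |
|---|---|---|---|---|
| 30% | 0.434 / 0.126 | 24.7% v 28.3% | 16.0 v 18.4 | 17.8% v 5.7% |
| 50% | 0.517 / 0.148 | 40.2% v 46.9% | 26.1 v 30.5 | 19.6% v 6.3% |
| 70% | 0.662 / 0.185 | 54.5% v 65.1% | 35.4 v 42.3 | 22.1% v 7.0% |

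With no deaths at all, the follow-up lost would be 15.9% v 5.1%. Within the 6-month window of the cost-effectiveness model, the loss runs from 8.4% v 2.6% (no deaths) to 13.5% v 4.0% (70% mortality).

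**Direction.** Unrecorded deaths and late adverse events in the ERCP arm make EUS look worse. Unrecorded resections in the ERCP arm make EUS look better. The biases do not all point the same way.

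**The case against.** **Safety reporting may catch some of this.** The serious adverse event definition covers any time after the procedure. The Participating sites section requires all fatal events to be reported within 24 hours, whether or not related, and all serious events to be collected. The Coordinating Center's report includes whether the subject is on or off study. This stands in part: some later deaths and serious events may arrive passively. It does not amount to scheduled ascertainment, and it does not cover EQ-5D, resource use or non-serious events.

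**The visit schedule runs to 1 year.** Data collection lists visits to that point without exception. It does not override the explicit stop rule under Follow-up.

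**Censoring could remove the distortion.** Under the model above, where death is independent of dysfunction, censoring at exit gives an unbiased mortality comparison, and the protocol does not fix the mortality analysis. That is correct, so the table applies to crude counts only. But the Discussion argues that re-intervention delays chemotherapy that carries a survival benefit. If so, dysfunction is related to prognosis and censoring at it is informative.

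**Stronger readings that the documents do not support.**

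- A reader might infer that the cost of dysfunction is lost. The hospital stay and chemotherapy delay of that episode are captured, and additional procedures are recorded. What is lost is cost and utility after the episode.
- A reader might infer that the surgery stop adds to the same imbalance. No surgery rates are given, so its direction between arms is unknown. It cannot cut resection short, because surgery is the event.
- The hypothesis that EUS is "associated with fewer episodes of stent dysfunction and need for re-intervention" might suggest a lost count of repeat episodes. The primary endpoint is powered as a proportion of patients, and no listed endpoint counts episodes. The chemotherapy item in Table 3 mentions recurrent dysfunction but is also a proportion of patients.
- "A decision tree will be created for the two possible biliary drainage approaches over a 6-month time horizon" might look like a further error beside 12 months of follow-up. It is a modelling choice that contradicts nothing, and the shorter window reduces the loss.

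**Conclusion.** The point holds for secondary and additional outcomes. The protocol ends scheduled follow-up at an event expected three times as often under ERCP, about 19.5 v 6.5 of 65 patients, while planning comparisons that need later data. With identical true mortality, crude recorded deaths would differ by about 4 percentage points (true 30%), 7 points (50%) or 11 points (70%), with fewer in the ERCP arm. These sizes rest on assumed mortality, constant hazards, the planned dysfunction rates, no surgery exits and no passive capture of deaths after exit. Passive capture would shrink them.

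A reader might conclude that the trial's main result is compromised. It is not: the dysfunction stop leaves the primary endpoint and time to first dysfunction intact, and technical success and most early events are little affected. This is a should-fix.

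**What to change.** Keep the first dysfunction as the primary endpoint. Amend Follow-up and Endpoints so that vital status, adverse events, surgery, hospitalisation, EQ-5D and resource use are collected to death or 12 months in every randomised patient, regardless of dysfunction or surgery. The phone contacts and chart review already described under Follow-up are sufficient.

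The cost is a protocol amendment and the remaining contacts for about 26 expected dysfunction patients plus those who have surgery. No new procedures are needed, and the sample size is unchanged. The amendment should be made while patients are under observation, since missed EQ-5D assessments in particular may be unrecoverable later.
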